### **Non-haematological**

Based on the most severe toxicity experienced since the last treatment, the following dose modifications should be used for non-haematological toxicities. The rest period should be extended until all non-haematological toxicities have subsided to Grade 1 or less, except increased bilirubin and ALAT which must recover to Grade 1 or baseline Grade, whichever is higher.

#### **Nausea and vomiting:**

For Grade 3 nausea and/or vomiting that occurs with suboptimal antiemetic therapy, treatment should be continued for the next course with an effective anti-emetic treatment and without dose modification. The administration of 5-HT3 antagonists (granisetron, ondansetron or variants) with corticosteroids (e.g. dexamethasone) is recommended for prevention and treatment of oxaliplatin-induced emesis.

#### **Diarrhea:**

If Grade 3 or 4 diarrhea occurs at any time, the doses should be reduced according to Table below. After Grade 3 or 4 diarrhea, the patient must have recovered to Grade 1 or less before treatment can be re-initiated.

#### **Stomatitis:**

After Grade 3 or 4 stomatitis, the doses should be reduced according to table below. The patient must have recovered to Grade 1 or less before treatment can be re-initiated.

#### **Cardiac toxicity:**

For Grade  $\geq 2$  cardiac toxicity which is attributable to 5-FU, patients will be permanently discontinued from 5-FU/LV therapy.

**Gastro-intestinal ulceration and bleeding:**

For Grade  $\geq 2$  gastro-intestinal toxicity which is attributable to 5-FU, treatment will be held until recovery to Grade  $\leq 1$ .

**Skin toxicity:**

Treatment will be held for Grade 3 or 4 toxicity until recovery to Grade  $\leq 1$ . Treatment may be withheld to allow for recovery. The extended rest period should not exceed 3 weeks from the scheduled administration. If the patient does not recover to Grade  $\leq 1$  in this timeframe, he/she will be taken off treatment.

**Non haematological toxicity scale – Oxaliplatin + 5-FU dose adjustment**

| TOXICITY                                                | Grade    | 5-FU bolus                 | 5-FU infusion              | Oxaliplatin                                           |
|---------------------------------------------------------|----------|----------------------------|----------------------------|-------------------------------------------------------|
| Allergic reactions                                      | $\geq 3$ | No dose reduce             | No dose reduce             | Stop treatment permanently                            |
| Respiratory symptoms indicative of pulmonary fibrosis   | any      | No dose reduce             | No dose reduce             | Interrupt treatment and investigate cause of symptoms |
| Interstitial pulmonary fibrosis not present at baseline | any      | No dose reduce             | No dose reduce             | Stop treatment permanently                            |
| Nausea and/or Vomiting                                  | $\geq 3$ | 200 mg/m       | 2000 mg/m      | 75 mg/m                                   |
| Diarrhea                                                | $\geq 3$ | 200 mg/m       | 2000 mg/m      | 75 mg/m                                   |
| Stomatitis                                              | 3        | 200 mg/m       | 2000 mg/m      | No dose reduce                                        |
| Stomatitis                                              | 4        | 0                          | 2000 mg/m      | 75 mg/m                                   |
| Cardiac toxicity (HF syndrome)                          | $\geq 3$ | Stop treatment permanently | Stop treatment permanently | Stop treatment permanently                            |
| Skin toxicity (HF syndrome)                             | $\geq 3$ | 200 mg/m       | 2000 mg/m      | No dose reduce                                        |
| The dose of leucovorin should remain identical          |          |                            |                            |                                                       |

### 6.2.3 Toxicity management guidelines for combination treatment regimen

Combination of Durvalumab, tremelimumab and FOLFOX has never been evaluated. Any potential overlapping toxicity may occur following treatment with this combination and will be difficult to assess. Toxicity will not be managed individually but will be managed according to the guidelines described in section 6.2.1 and 6.2.2 and both treatments will be adjusted simultaneously.

## **7. RESTRICTIONS DURING THE STUDY AND CONCOMITANT TREATMENT(S)**

### **7.1 Restrictions during the study**

Females of childbearing potential who are sexually active with a non-sterilized male partner must use 2 methods of effective contraception (Table 1) from the time of screening and must agree to continue using such precautions for 180 days after the last dose of durvalumab + tremelimumab combination therapy or 90 days after the last dose of durvalumab monotherapy, whichever is the longer time period; cessation of birth control after this point should be discussed with a responsible physician. Periodic abstinence, the rhythm method, and the withdrawal method are not acceptable methods of birth control.

- Females of childbearing potential are defined as those who are not surgically sterile (ie, bilateral tubal ligation, bilateral oophorectomy, or complete hysterectomy) or post-menopausal (defined 12 months with no menses without an alternative medical cause).
- Non-sterilized males who are sexually active with a female partner of childbearing potential must use 2 acceptable methods of effective contraception (see Table 1) from screening through 180 days after receipt of the final dose of durvalumab + tremelimumab combination therapy or 90 days after receipt of the final dose of durvalumab monotherapy, whichever is the longer time period.

Restrictions relating to concomitant medications are described in Section 7.2.

**Table 1. Effective methods of contraception (2 methods must be used)**

| Barrier methods      | Intrauterine device methods                                            | Hormonal methods            |
|-----------------------------|-------------------------------------------------------------------------------|------------------------------------|
| Male condom plus spermicide | Copper T                                                                      | Implants                           |
| Cap plus spermicide         | Progestosterone T a                                                | Hormonal shot or injection         |
| Diaphragm plus spermicide   | Levonorgestrel-releasing
intrauterine system
(eg, Mirena®) a | Combined pill
Minipill
Patch |

a This is also considered to be a hormonal method.

### **Blood donation**

Subjects should not donate blood while participating in this study or for at least 90 days following the last infusion of durvalumab or tremelimumab or until the time specified in the prescribing information of FOLFOX.

### **7.2 Concomitant treatment(s)**

The Principal Investigator must be informed as soon as possible about any medication taken from the time of screening until the end of the clinical phase of the study (final study visit). Any concomitant medication(s), including herbal preparations, taken during the study will be recorded in the CRF.

Restricted, prohibited, and permitted concomitant medications are described in the following tables. Refer to Section 6.6 for guidance on management of IP-related toxicities.

### **7.2.1 Permitted concomitant medications**

Investigators may prescribe concomitant medications or treatments (e.g., acetaminophen, diphenhydramine) deemed necessary to provide adequate prophylactic or supportive care except for those medications identified as “excluded” as listed in Section 7.2.2.

### **7.2.2 Excluded Concomitant Medications**

The following medications are considered exclusionary during the study.

1. Any investigational anticancer therapy other than the protocol specified therapies (Durvalumab, tremelimumab and FOLFOX are allowed)
2. Any concurrent chemotherapy, radiotherapy (except palliative radiotherapy), immunotherapy, biologic or hormonal therapy for cancer treatment, Concurrent use of hormones for noncancer-related conditions (e.g., insulin for diabetes and hormone replacement therapy) is acceptable. Local treatment of isolated lesions for palliative intent is acceptable (e.g., by local surgery or radiotherapy)
3. Immunosuppressive medications including, but not limited to systemic corticosteroids at doses not exceeding 10 mg/day of prednisone or equivalent, methotrexate, azathioprine, and TNF- $\alpha$  blockers. Use of immunosuppressive medications for the management of investigational product-related AEs or in subjects with contrast allergies is acceptable. In addition, use of inhaled and intranasal corticosteroids is permitted. <>
4. Live attenuated vaccines within 30 days of durvalumab and tremelimumab dosing (ie, 30 days prior to the first dose, during treatment with durvalumab and tremelimumab for 30 days post discontinuation of durvalumab and tremelimumab. Inactivated vaccines, such as the injectable influenza vaccine, are permitted.
5. Patient with large blood vessel invasion are at higher risk for bleeding and any agents affecting platelet function/coagulation should be avoided (Aspirin, NSAIDS...)

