| Any concurrent chemotherapy, local therapy (except palliative radiotherapy for non-target lesions, eg, radiotherapy, surgery, radiofrequency ablation), biologic therapy, or hormonal therapy for cancer treatment           | Should not be given whilst the patient is on IP treatment (including SoC). (Concurrent use of hormones for non-cancer-related conditions [eg, insulin for diabetes and hormone replacement therapy] is acceptable.)                                                                            |
| Immunosuppressive medications, including, but not limited to, systemic corticosteroids at doses exceeding 10 mg/day of prednisone or its equivalent, methotrexate, azathioprine, and tumor necrosis factor $\alpha$ blockers | Should not be given whilst the patient is on IP treatment (including SoC). (Use of immunosuppressive medications for the management of IP-related AEs or in patients with contrast allergies is acceptable. In addition, use of inhaled, topical, and intranasal corticosteroids is permitted. |
| Live attenuated vaccines                                                                                                                                                                                                     | Should not be given through 30 days after the last dose of IP (including SoC) during the study                                                                                                                                                                                                 |

| Rescue/supportive medication/class of drug:                                                                                                                                                                                             | Usage:                                        |
|------------------------------------------------------------------------------------------------------------------------------------------------------------------------------------------------------------------------------------------------|------------------------------------------------------|
| Concomitant medications or treatments (eg, acetaminophen or diphenhydramine) deemed necessary by the Investigator to provide adequate prophylactic or supportive care, except for those medications identified as “prohibited” as listed above | To be administered as prescribed by the Investigator |

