| Best supportive care (including antibiotics, nutritional support, growth factor support, correction of metabolic disorders, optimal symptom control, and pain management [including palliative radiotherapy, etc])                             | Should be used when necessary for all patients       |
| Best supportive care (including antibiotics, nutritional support, growth factor support, correction of metabolic disorders, optimal symptom control, and pain management [including palliative radiotherapy, etc])                             | Should be used when necessary for all patients       |

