## Evaluation of target lesions

|                         |                                                                                                                                                                                        |
|-------------------------|----------------------------------------------------------------------------------------------------------------------------------------------------------------------------------------|
| Complete Response (CR): | Disappearance of all target lesions.                                                                                                                                                   |
| Partial Response (PR):  | At least a 30% decrease in the sum of LD of target lesions taking as reference the baseline sum LD.                                                                                    |
| Progression (PD):       | At least a 20% increase in the sum of LD of target lesions taking as references the smallest sum LD recorded since the treatment started or the appearance of one or more new lesions. |
| Stable Disease (SD):    | Neither sufficient shrinkage to qualify for PR nor sufficient increase to qualify for PD taking as references the smallest sum LD since the treatment started.                         |

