### **11.3.2. Efficacy Analyses set**

Efficacy analyses will be performed in modified intent-to-treat population (ITT) population ie, all patients following the major inclusion criteria and with a 3 months evaluation. Analyses will be repeated in the intent to treat principle i.e including all enrolled patients whatever eligibility criteria and treatment received patients and in the per protocol population (patients who had received all the planned doses).

The primary objective will be evaluated at 3 months among MSS patients only. According to the Simon's design, at 3 months, on the first evaluable 43 patients (mITT population): if 26 or more patients respond to treatment the treatment will be considered of interest for evaluation in a phase III trial. Response rates will be evaluated using RECIST criteria. Response will be considered for patient with Complet response (CR), partial response (PR) and stable disease (SD). Overall survival and progression free survival (OS and PFS) will be estimated using Kaplan Meier method. Median survivals will be reported with 95% confidence intervals (CI).

Median follow-up will be estimated using the reverse Kaplan Meier method.

Analysis of survival and response among MSI patients will be performed in an exploratory manner, taken into account the small sample size in this population. All statistical analysis will be performed with Stata 11 or SAS 9.3.

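### Section 7.2.2 and its Table 2 give different rules on palliative local treatment of lesions, and the difference can reach the primary response count

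*Protocol*

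**What the plan says.** Three places in the Protocol govern local treatment of lesions during the study.

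- Section 7.2.2, item 2, excludes "Any concurrent chemotherapy, radiotherapy (except palliative radiotherapy), immunotherapy, biologic or hormonal therapy for cancer treatment". It then adds "Local treatment of isolated lesions for palliative intent is acceptable (e.g., by local surgery or radiotherapy". The permission is limited to palliative intent but not by lesion type.
- Table 2, prohibited part, lists "Any concurrent chemotherapy, local therapy (except palliative radiotherapy for non-target lesions, eg, radiotherapy, surgery, radiofrequency ablation". The usage column says "Should not be given whilst the patient is on IP treatment (including SoC".
- Table 2, supportive-care row, allows best supportive care for all patients when needed, including "pain management [including palliative radiotherapy, etc". It does not repeat the non-target limit.

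Section 7.2 refers the reader to the tables, while Section 7.2.1 refers the reader to the exclusions in Section 7.2.2. No order of precedence is stated.

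On the endpoint, Section 9.1.2 defines complete response of target lesions as "Disappearance of all target lesions" and partial response as a fall of at least 30% in their summed longest diameters. Section 11.3.2 applies this to the decision: "Response will be considered for patient with Complet response (CR), partial response (PR) and stable disease (SD". The cut-offs are at least 9 of 16 at the interim (Section 11.3.4) and at least 26 of 43 at the end (Section 11.3.2).

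**The concern.** An investigator who wants to palliate a symptomatic lesion gets one answer from the text and another from the table. For target lesions the choice affects more than patient care. The go/no-go count depends on target-lesion size, and stable disease is enough for success. If such a lesion is removed or irradiated before the Cycle 6 scan, a smaller or unchanged sum may reflect the local procedure and not durvalumab, tremelimumab and FOLFOX. A single-arm design has no control group in which the same thing would also happen. Any distortion from masked failures pushes the count upwards, and its extent would depend on which list each site follows.

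**Working it through.** **1. The passages side by side**

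| Procedure, palliative intent | 7.2.2 item 2 | Table 2, prohibited | Table 2, supportive care |
|---|---|---|---|
| Surgery, isolated target lesion | accepted | prohibited | not mentioned |
| Surgery, isolated non-target lesion | accepted | prohibited | not mentioned |
| Radiotherapy, target lesion | accepted | prohibited | listed, no limit stated |
| Radiotherapy, non-target lesion | accepted | excepted from the ban | listed, no limit stated |

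The text and the prohibited list agree only in the last row. Table 2 also bars radiofrequency ablation, which item 2 does not name.

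**2. How a treated target lesion enters the count**

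Section 4.1, criterion 9, requires only one measurable lesion, and the comparison table in Section 9.2 allows up to five target lesions. Taking lesions of equal size (an assumption):

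- One target lesion, removed: the sum falls by 100%.
- Two, one removed: the sum falls by 1/2 = 50%, beyond the 30% needed for partial response.
- Five, one removed: the sum falls by 1/5 = 20%. The other four would have to grow by 50% before the total reached 120% of baseline (0.8 × 1.5 = 1.2), so smaller growth would be read as stable disease.

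In each case this holds only if there is no new lesion and no non-target progression.

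**3. The plan's own operating characteristics**

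Inputs from Sections 11.3.2, 11.3.4 and 11.4: p0 = 0.50, p1 = 0.707, α = 10%, power = 90%, continue at ≥9/16, success at ≥26/43 (27 further patients in stage 2).

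P(go | p) = Σ over x = 9 to 16 of P(X = x; 16, p) × P(Y ≥ 26 − x; 27, p)

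- p = 0.50: 0.0931, within the stated 10%.
- p = 0.707: 0.9014, matching the stated 90%.

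The design reproduces. Ignoring the first stage, P(≥26 of 43) at p = 0.50 is 0.111, but that is not the error rate of this two-stage rule.

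**4. Illustration of masking**

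Suppose that, in expectation, k true failures among 43 are counted as successes because a target lesion was locally treated, spread evenly over both stages. The counted rate under the null becomes 0.50 + k/43.

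| Expected masked failures | Counted rate | P(go) |
|---|---|---|
| 0 | 0.5000 | 0.0931 |
| 1 | 0.50 + 1/43 = 0.5233 | 0.1524 |
| 2 | 0.50 + 2/43 = 0.5465 | 0.2322 |

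The values of k are assumed; the documents give none.

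**The case against.** The strongest reply is that the wording conflict is real but its route to the decision is narrow.

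- Criterion 34 of Section 4.2 excludes resectable disease, so surgery on a patient's only measurable lesion within three months should be rare. This stands, although it does not rule out palliative radiotherapy or a limited palliative procedure.
- New lesions or unequivocal non-target progression are progression whatever happens to the target lesion (Section 9.1.2), and Section 9.3 lets symptomatic progression set the PFS date. Some patients who need palliation would therefore be recorded as progressing. This stands as a partial safeguard.
- The schedule footnote on imaging asks for a confirmatory scan for complete or partial response. This helps less, because stable disease already counts as success.
- The supportive-care row of Table 2 can be read together with the prohibition above it, as palliative radiotherapy to non-target lesions only. This is a fair reading. The firm contradiction is between item 2 and the prohibited list; the supportive-care row only needs its limit stated.

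A reader might also infer that the plan has no way to handle a locally treated target lesion, or that every such patient must be a non-success. The document does not support either inference. Section 9.1 calls its criteria a quick reference, a counting rule may sit in the statistical analysis plan, which is not at hand, and counting such patients as failures is only one of several defensible choices. An analysis plan could not, however, make two instructions to sites agree.

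**Conclusion.** The contradiction is certain: palliative surgery on an isolated lesion, and palliative radiotherapy to a target lesion, are each accepted in item 2 of Section 7.2.2 and prohibited in Table 2. Item 2 is confined to palliative intent, and Table 2 bars surgery and ablation of any lesion, not only of target lesions.

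The effect on the decision is possible but unquantified. A false-go probability of 15.2% or 23.2%, against 9.3% for the design as written, assumes an expected one or two masked failures among 43 and shows only how sensitive the cut-off is. A reader might infer that the trial's type I error is actually inflated to those levels. The documents do not support that, because they give no frequency of local treatment and the safeguards above would remove some cases. The point is a site-facing inconsistency worth correcting because it touches the primary count. It is not a fault in the Simon design, whose stated error rates reproduce.

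**What to change.** Reconcile item 2 of Section 7.2.2 with the prohibited and supportive-care rows of Table 2 so that one rule on local treatment applies, stated separately for target and non-target lesions. Which clinical rule applies is for the sponsor to decide.

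Add an eCRF flag for any local treatment of a target lesion before the 3-month evaluation, with its date and type. The effect on the primary count can then be examined, for example by a sensitivity analysis that does not credit response on a treated target lesion. That analysis may be specified in the statistical analysis plan.

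The cost is a few lines of protocol text and one data item. The sample size and the cut-offs do not change, and the flag and the sensitivity analysis restrict no patient's care.

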## 4.2 Exclusion criteria

Subjects should not enter the study if any of the following exclusion criteria are fulfilled:

- 1 Involvement in the planning and/or conduct of the study (applies to both AstraZeneca staff and/or staff at the study site). Previous enrolment in the present study,
- 2 Participation in another clinical study with an investigational product during the last 4 weeks,
- 3 Any previous treatment with a PD1 or PD-L1 inhibitor, including durvalumab or an anti-CTLA4, including tremelimumab (Unless prior PD1/PD-L1 or CTLA-4 inhibition is a specific entry criterion)
- 4 History of another malignancy within the 5 previous years with low potential risk for recurrence other than :
  - *Adequately treated non-melanoma skin cancer or lentigo maligna without evidence of disease*
  - *Adequately treated carcinoma in situ without evidence of disease eg, cervical cancer in situ*
- 5 Receipt of the last dose of anti-cancer therapy (chemotherapy, immunotherapy, endocrine therapy, targeted therapy, biologic therapy, tumor embolization, monoclonal antibodies, other investigational agent) 28 days prior to the first dose of study drug (14 days prior to the first dose of study drug for subjects who have received prior TKIs (e.g., erlotinib, gefitinib and crizotinib) and within 6 weeks for nitrosourea or mitomycin C).
- 6 Mean QT interval corrected for heart rate (QTc)  $\geq 470$  ms calculated from 3 electrocardiograms (ECGs) using Frediricia's Correction,
- 7 Current or prior use of immunosuppressive medication within 28 days before the first dose of durvalumab or tremelimumab, with the exceptions of intranasal and inhaled corticosteroids or systemic corticosteroids at physiological doses, which are not to exceed 10 mg/day of prednisone, or an equivalent corticosteroid
- 8 Any history of hypersensitivity to durvalumab, tremelimumab, FOLFOX or their excipients,
- 9 Any unresolved toxicity (CTCAE grade  $>1$ ) from previous anti-cancer therapy. Subjects with irreversible toxicity that is not reasonably expected to be exacerbated by the investigational product may be included (e.g., hearing loss, peripherally neuropathy)
- 10 Any prior Grade  $\geq 3$  immune-related adverse event (irAE) while receiving any previous immunotherapy agent, or any unresolved irAE  $>$ Grade 1 ,

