### **5.3.3 Monitoring of dose administration**

Dose reductions during treatment should be based on adverse events. Oxaliplatin administration does not require hyperhydration. In the event of extravasation, administration must be discontinued immediately. For nausea and vomiting, 5-HT3 antagonists with or without dexamethasone are strongly recommended for oxaliplatin-based chemotherapy. Oxaliplatin must be infused either by peripheral vein or central venous line over 2 hours. The infusion line must be adequately flushed with 5% dextrose solution (D5W) between oxaliplatin infusion and the administration of any other drug. If desired, oxaliplatin can be administered concurrently (via a Y-connector from separate bags and lines) with leucovorin, given as a 2-hour IV infusion in 250 ml dextrose 5%, but should not be administered concurrently with 5-FU.

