**Allergic reactions:**

For Grade 1 or 2 acute hypersensitivity reactions, no dose modification of oxaliplatin is required if, in the investigator's opinion, it is in the patient's best interest to continue. Pre-medication with dexamethasone 20 mg IV, diphenhydramine 50 mg IV, and one of the following: cimetidine 300 mg IV, ranitidine 50 mg IV, or famotidine 20 mg IV 30 minutes prior to study drug administration is suggested. If an allergic reaction persists into the next cycle, administer 50 mg dexamethasone PO 12 hours and 6 hours prior to administration of oxaliplatin. For Grade 3 or 4 acute hypersensitivity reactions, treatment with oxaliplatin should be discontinued.

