| 
 
• Inability to reduce corticosteroid to a dose of <math>\leq 10</math> mg of prednisone per day (or equivalent) within 12 weeks of the start of the immune-mediated adverse event (imAE)
 
• Grade 3 recurrence of a previously experienced treatment-related imAE following resumption of dosing
 
 | 
 
– Whether specific immune-mediated events (and/or laboratory indicators of such events) are noted in these guidelines or not, patients should be thoroughly evaluated to rule out any alternative etiology (e.g., disease progression, concomitant medications, and infections) to a possible immune-mediated event. In the absence of a clear alternative etiology, all such events should be managed as if they were immune related. General recommendations follow.
 
                                                                                            |
| 
Grade 1 No dose modification
 
Grade 2 Hold study drug/study regimen dose until Grade 2 resolution to Grade <math>\leq 1</math>.
                                                                                                                                                                                                        | 
 
– Symptomatic and topical therapy should be considered for low-grade (Grade 1 or 2, unless otherwise specified) events.
 
                                                                                                                                                                                                                                                                                                                                                                                                                                           |

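### Section 7.2.2 item 3 states the steroid limit the wrong way round: it excludes prednisone up to 10 mg/day, which Table 2 and exclusion criterion 7 allow

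*Protocol*

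**What the plan says.** The protocol sets a limit of 10 mg/day prednisone or equivalent in several places.

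- **Section 7.2.2, item 3.** The section opens by declaring the items on its list not allowed during the study. Item 3 begins: "Immunosuppressive medications including, but not limited to systemic corticosteroids at doses not exceeding 10 mg/day of prednisone or equivalent". It then exempts treatment of adverse events caused by the investigational product, use in contrast allergy, and inhaled or intranasal steroids. It ends by allowing a temporary steroid course at the investigator's discretion and gives nausea as one example.
- **Table 2, immunosuppressive row.** The prohibited range is "systemic corticosteroids at doses exceeding 10 mg/day of prednisone or its equivalent".
- **Exclusion criterion 7, in section 4.2 and again in the Synopsis.** Among the exceptions to the ban on recent immunosuppression are "systemic corticosteroids at physiological doses, which are not to exceed 10 mg/day of prednisone, or an equivalent corticosteroid".
- **Section 7.2.1.** Prophylactic and supportive drugs may be given unless they stand on the 7.2.2 list.
- **Appendix 1, general considerations.** One reason for permanent discontinuation is "Inability to reduce corticosteroid to a dose of" 10 mg of prednisone per day or less within 12 weeks of the start of an immune-mediated event.

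**The concern.** The same threshold points in opposite directions within one section. Under Table 2, steroids become a problem above 10 mg/day. Under item 3 as printed, doses up to 10 mg/day are the problem. A patient can satisfy exclusion criterion 7 on a low maintenance dose, be enrolled correctly, and then be on a barred drug from the first day of treatment.

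At stake is what sites and monitors do. One site could withdraw a long-standing low-dose steroid and another could continue it; one monitor could record a deviation and another none. Steroid exposure matters clinically in a trial of two checkpoint inhibitors, so the rule that governs it should have one direction.

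**Working it through.** There is no figure to recompute. The check is to read each rule for a continuing systemic steroid that none of the exceptions covers.

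| Rule | Up to 10 mg/day | Above 10 mg/day |
|---|---|---|
| 7.2.2 item 3, as printed | excluded | not named by the dose phrase, but the list of immunosuppressants is open-ended |
| Table 2 | outside the prohibited range | prohibited |
| Exclusion criterion 7 (at entry) | admitted, at physiological doses | excluded if used within 28 days before the first dose |
| 7.2.2 item 3 with *not* deleted | outside the excluded range | excluded |

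**Step 1: direction.** In the first column, item 3 disagrees with both other rules. With *not* deleted, it agrees with both.

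**Step 2: how many independent rules oppose item 3.** Two do: Table 2 and exclusion criterion 7. The criterion is printed twice (Synopsis and section 4.2) but is one rule. Appendix 1 uses 10 mg/day as a ceiling in four places, but those concern steroids given for immune-mediated events, which item 3 exempts. They show which direction was intended and do not themselves conflict with item 3.

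**Step 3: which text governs.** The introduction to section 7.2 says that the tables describe what is prohibited and permitted, which favours Table 2. Section 7.2.1 instead makes the 7.2.2 list the boundary for supportive drugs, and item 3 is on that list. The protocol has no rule of precedence between the two.

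**Step 4: who is caught.** Start from patients on a systemic steroid of up to 10 mg/day. Remove those treated for an adverse event of the investigational product or for contrast allergy (item 3), those on a temporary course allowed by the investigator (item 3), and those on hormone replacement for a condition other than cancer (item 2). What remains are patients on a continuing low-dose systemic steroid for some other chronic reason. The protocol gives no frequency for this group.

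**Step 5: reach into the analysis.** The modified intent-to-treat set depends on the major inclusion criteria and a 3-month evaluation, and the per-protocol set on having received all planned doses (sections 11.2.2 and 11.3.2). Neither refers to concomitant steroids. The decision rules (9 or more responders among 16, then 26 or more among 43) and the sample size (52 patients with MSS disease, 57 in all) do not depend on them either.

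**The case against.** The strongest reply is that nobody would be misled. Read literally, item 3 bars a small dose while its dose phrase does not name a large one, so the slip is obvious. Section 7.2 points to the tables, Table 2 has the direction right, and the exceptions leave few patients exposed. Most of this stands: the intention is clear and the group is probably small. It does not remove the contradiction, because section 7.2.1 sends the reader to the list that contains the error, and a monitor is not free to correct operative text by inference.

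Two stronger readings may tempt a reader, and the documents support neither.

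- **That the protocol both forbids and recommends dexamethasone with oxaliplatin.** Section 5.3.3 says 5-HT3 antagonists "with or without dexamethasone are strongly recommended for oxaliplatin-based chemotherapy", section 6.2.2 says that combining them "with corticosteroids (e.g. dexamethasone) is recommended for prevention and treatment of oxaliplatin-induced emesis", and the allergy paragraph of 6.2.2 suggests "Pre-medication with dexamethasone 20 mg IV, diphenhydramine 50 mg IV", while the steroid row of Table 2 names no such exception. But item 3 allows temporary steroids at the investigator's discretion, names nausea, and leaves its list of indications open. The recommendations in 5.3.3 and 6.2.2 are specific, and Table 2 says of best supportive care, which includes symptom control, "Should be used when necessary for all patients". The protocol as a whole therefore does not ban antiemetic dexamethasone. That Table 2 does not repeat an allowance printed just before it is an editorial difference. The angle brackets around the allowance are no reason to disregard it, since similar marks appear at operative text in sections 10.1.5, 10.2 and 10.2.2.1.
- **That item 3 as printed permits high-dose steroids.** Its opening is open-ended, so the class stays excluded, and Table 2 prohibits doses above the limit outright.

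**Conclusion.** The point holds as a contradiction in an operative rule. Item 3 of section 7.2.2 inverts the limit that Table 2 and exclusion criterion 7 both set. Its consequence is limited to site conduct and deviation classification, for patients on a continuing low-dose systemic steroid outside the listed exceptions. That group is probably small; this is a judgement from the breadth of the exceptions, since the protocol gives no count. Primary endpoint, decision rules, analysis sets and sample size are untouched. The correction is worth making because the two texts cannot both be followed and the intended direction is not in doubt.

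**What to change.** In section 7.2.2 item 3, change *not exceeding* to *exceeding*, so that it agrees with Table 2. Judge steroid deviations against that rule, including any already recorded under the printed text. No new exception in Table 2 is needed for dexamethasone with oxaliplatin.

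The cost is one deleted word and a short notice to sites. Nothing is given up: the 10 mg/day limit stays, the existing exceptions stay, and no analysis changes.
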